## Discussion

This study protocol describes a three-arm parallel-group randomized controlled trial to investigate several potentially effective components of feedback from ROM in youth mental health care in the Netherlands. It is hypothesized that the more specific and concrete the feedback, the more and faster children’s and adolescents’ symptoms will decrease, the more children’s and adolescents’ quality of life will improve and the more children, adolescents and parents will be satisfied at the end of treatment. In addition, we expect to find a negative relationship between feedback condition and the duration of treatment. It is hypothesized that the more specific and concrete the feedback, the fewer sessions treatments will contain and the shorter treatments will be. Also, we expect that children, adolescents and parents will drop out of treatment less often when feedback is more specific and concrete. We expect that the largest effects of feedback will occur when clinicians additionally discuss the feedback with a colleague. Finally, we expect that feedback will be most effective for children and adolescents who are not progressing well in treatment.

### Strengths and limitations

One of the strengths of this study is that we operationalize and directly compare three different forms of feedback to improve the design and delivery of feedback. The feedback conditions are derived directly from feedback theories and, to the best of our knowledge, the current study is the first to assess the effects of enhancing feedback with case consultation. Second, we focus not only on the effectiveness of different components of feedback, but also on the mechanisms through which feedback possibly works. We aim to understand why feedback is effective in some cases but not in others by testing whether not progressing well in treatment (i.e. not on track) moderates the effects of feedback. Third, we specifically investigate the effects of feedback in youth mental health care. We are thereby contributing to the limited knowledge about the effects of feedback and the importance of specific aspects of feedback for this particular population. Fourth, we actively involve parents in the study and combine self-reports with parent-reports. For children between 4 and 11 years old, parents fill out the questionnaires and clinicians will discuss the feedback with the parents. Hence, it is possible to assess the effects of different forms of feedback for young children and when only parents are receiving help (i.e. parenting skills training). Fifth, our study takes place in real-world clinical practice. The participating children, adolescents and parents are diverse in socio-demographic characteristics (e.g. sex, age, educational level, ethnicity, socioeconomic status, marital status and household composition) and the children and adolescents have all kinds of mental health problems. The study has only one exclusion criterion (insufficient understanding of the Dutch language). The results of the study will, therefore, have good external validity.

A limitation of the study is that differences in the care provided to participants in the second and third feedback conditions other than the intervention can arise (performance bias), because the intervention will be focused on the clinician. Since clinicians will not be blinded, it is possible that they will make additional efforts to improve treatment outcome when they receive feedback reports from the second and third feedback conditions instead of the first condition (control condition). Besides that, it is possible that effects from the third feedback condition will spill over to the second feedback condition. If clinicians have discussed several feedback reports with their colleagues (third feedback condition), they might guess what reactions their colleagues would have and what advice they would offer for clients who are not discussed (second feedback condition). Because each clinician will only have a couple of clients in each feedback condition, we think that such a spillover effect is unlikely. Furthermore, clients in the second and third feedback conditions may experience a placebo effect if their clinicians reveal that their feedback reports are being discussed with a colleague to improve treatment. In addition, due to technical and logistic restrictions, we are unable to check whether clinicians actually discuss the feedback with the children, adolescents and parents. However, we will remind the clinicians to discuss the feedback by sending them e-mail messages and we will ask clients at each measurement whether the feedback was discussed. Lastly, due to financial constraints, we will be unable to investigate the long-term effects of feedback in youth mental health care. Hence, further research should include follow-up measurements after treatment has ended.

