[48,49]. However, youth departments of mental health care institutions treat children and adolescents of all ages and we would like to generalize the results of this study to all age groups. To ensure that the distribution of parents and children and adolescents is similar in the three feedback conditions, randomization will be stratified by age of the child or adolescent (4 to 11 years old and 12 to 17 years old).

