### Outcome measures

#### Primary outcome measure

The primary outcome measure will be symptom severity, which will be measured with the Dutch version of the Strengths and Difficulties Questionnaire (SDQ
[53,54]). The SDQ will be filled out by parents when the child is between 4 and 11 years old and by children or adolescents when they are between 12 and 17 years old. For the first assessment, the extended versions of the SDQ for both parents and children and adolescents will be used. Each version consists of 25 items on strengths and difficulties and an additional impact supplement. The 25 items are scored on a 3-point scale ranging from 0 (not true) to 2 (completely true). These items are divided into five subscales: emotional symptoms, conduct problems, hyperactivity-inattention, peer relationship problems and prosocial behaviour. A total difficulties score can also be calculated by summing the scores on the emotional symptoms, conduct problems, hyperactivity-inattention, and peer problems subscales (total score can range from 0 to 40). The impact supplement asks whether the respondent thinks the child or adolescents has a problem, and, if so, inquires further about chronicity, distress, social impairment, and burden to others. For the measurements during treatment, the follow-up versions of the SDQ for both parents and children and adolescents will be used. These versions include the 25 items on strengths and difficulties, the impact question and two additional follow-up questions (‘Has the intervention reduced problems?’ and ‘Has the intervention helped in other ways, e.g. making the problems more bearable?’). The parent- and self-report versions of the SDQ have shown acceptable internal consistency, test-retest stability, and parent-youth agreement and good concurrent validity in a Dutch community sample
[54,55]. However, reliability seems insufficient for two subscales of the parent version – conduct problems and peer relationship problems
[56]. Therefore, the total difficulties score of the parent- and self-report versions will be used in the analyses.

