### Sample size calculation

Literature indicates various effect sizes of feedback from ROM
[17,21,27,62]. The present study was powered to detect the upper limit of a small effect size (f = 0.15; ANCOVA). A power analysis using G*Power
[63] indicated that a total sample size of 432 (n = 144 per condition) would be sufficient to detect significant (α = .05, power = .80) condition effects on symptom severity (3 conditions, including testing for 3 covariates and possible interaction effects).

However, our previous experiences have shown that approximately 50% of the participants stop filling out questionnaires after one measurement (baseline assessment). Hence, the clinicians of these children, adolescents and parents do not receive feedback during treatment. It would not be desirable to impute 50% of the data as this would make the imputation highly unreliable. Therefore, we will invite twice as many children, adolescents and parents (n = 288 per condition and 864 in total) to include the required number of 144 participants per condition of whom clinicians have received feedback during treatment (i.e. at least 50% of the measurements).

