### Statistical analyses

All analyses will be conducted using Mplus
[64], because this program allows analyses of complex data while taking into account the longitudinal character of the data. Intervention effects will be analyzed according to the intention-to-treat principle and the completers-only framework. For the intention-to-treat analysis, missing data will be handled using multiple imputations (MI). Descriptive statistics will be calculated for all variables of interest (e.g. symptoms, quality of life, satisfaction with treatment, number of sessions, length of treatment, dropout rate). In order to assess whether randomization resulted in equal groups, we will examine whether there are differences among the three feedback groups on relevant covariates (e.g. sex, age, educational level, ethnicity, socioeconomic status, marital status, household composition and diagnosis) using ANOVA for the continuous variables and Chi-Square tests for the categorical variables. Variables that are distributed differently among the three groups will be entered as control variables in all models testing the effects of the feedback conditions. The hypotheses will be tested using multivariate linear regression analyses. In addition, we will examine whether being NOT moderates the association between the feedback intervention and symptom severity. Therefore, interaction terms will be calculated as the product of the feedback condition and whether or not the client is NOT. These terms will be added as a second step in the multivariate analyses. Reporting of the results of the study will be in accordance with the CONSORT statement
[65,66].

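### Age group sets the SDQ informant and the feedback form, yet the described analysis neither always adjusts for it nor estimates effects by age group, so the claim about young children and parent-only help has no matching analysis

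*Protocol article*

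**What the plan says.** All references are to the protocol article.

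- **Informant.** Primary outcome measure: "The SDQ will be filled out by parents when the child is between 4 and 11 years old"; from 12 to 17 the child or adolescent fills it out. The total difficulties score from either version is the analysed outcome.
- **Feedback content.** Intervention: in conditions 2 and 3, parents complete the TSM-P (five domains) and youths the TSM-Y (four domains). The enhanced report is built from whichever form applies.
- **Handling of age.** Participants: the authors acknowledge that informants differ systematically in how they report symptoms, add that "we would like to generalize the results of this study to all age groups", and respond by stratifying the randomisation by age group. Randomization confirms this stratum alongside department.
- **Analysis.** Statistical analyses: "The hypotheses will be tested using multivariate linear regression analyses". Background variables, age among them, become control variables only if they turn out to differ between arms. The one interaction described is condition by not-on-track (NOT) status, which is also the only moderator named under Moderator and potential covariates.
- **Claims.** Strengths and limitations: "we actively involve parents in the study and combine self-reports with parent-reports", and "it is possible to assess the effects of different forms of feedback for young children and when only parents are receiving help".
- **Size.** Sample size calculation: the study was "powered to detect the upper limit of a small effect size (f = 0.15; ANCOVA"), and "a total sample size of 432 (n = 144 per condition) would be sufficient" at α = .05 and power .80. It allows for three covariates and possible interactions, without naming either.

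**The concern.** Age group carries several things at once: who rates the outcome, which obstacles the enhanced report covers, and who discusses the report. Stratified randomisation balances these across arms, so the pooled comparison is not biased by them. It does not put age group into the model, and it does not show whether the condition effect is similar under parent report and under self-report.

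Two things follow. First, the rule for choosing covariates works against the stratification: the better the stratification works, the less likely age group is to enter the model. Any informant difference in SDQ level not absorbed by another covariate then stays in the residual variance and costs precision. Second, one averaged effect cannot tell a reader whether feedback helped young children, whether it helped only one age group, or whether an effect in one group was diluted by the other. The Discussion presents the first of these as something the study can assess.

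**Working it through.** **1. Match between claim and analysis.**

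| Element | Ages 4-11 | Ages 12-17 | Described analysis |
|---|---|---|---|
| SDQ rater | parent | youth | one total score, no informant term named |
| Enhanced report | TSM-P, five domains | TSM-Y, four domains | one condition effect |
| Age group in model | – | – | only if unbalanced between arms |
| Condition by age group | – | – | not named; only condition by NOT |

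Each client has one informant, fixed by age. The two kinds of report are therefore combined across clients, never within a client.

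**2. Parent-only help.** The covariates listed do not include who receives help. The parenting-skills version of the Jeugdthermometer is completed only at the end of treatment. The question about the parent's own therapist is described with the TSM-P, which condition 1 does not receive. Neither gives a baseline marker in all three arms. The patient file might, but the article does not say so.

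**3. The plan's own figure.** Inputs from Sample size calculation: f = 0.15, α = 0.05, three conditions, three covariates. Non-central F with λ = N f², df1 = 2, df2 = N − 3 − 3.

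N = 432: λ = 432 × 0.0225 = 9.72, df2 = 426, power = 0.8007. The smallest N reaching 0.80 is 432, so the stated figure reproduces exactly.

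**4. The same test inside the 4-11 group.** The age split is not given; the shares below are assumptions.

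| Assumed share of 432 | N | λ = N × 0.0225 | Power at f = 0.15 |
|---|---|---|---|
| 30% | 130 | 2.93 | 0.31 |
| 40% | 173 | 3.89 | 0.40 |
| 50% | 216 | 4.86 | 0.486 |
| 60% | 259 | 5.83 | 0.57 |
| 70% | 302 | 6.80 | 0.64 |

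Whatever the split, the smaller age group has at most about 0.49. At N = 216 the smallest effect detectable with 80% power is f = 0.213, against 0.150 at N = 432.

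**5. Precision of a pairwise contrast.** The 95% CI half-width in residual SDs is 1.96 × √(2/n per arm).
- Pooled, n = 144: 1.96 × √(2/144) = 0.23.
- Half the sample, n = 72: 1.96 × √(2/72) = 0.33.
- 30% share, n = 43.2: 1.96 × √(2/43.2) = 0.42.
- 70% share, n = 100.8: 1.96 × √(2/100.8) = 0.28.

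**6. What an interaction test could show.** Illustration: f = 0.15 in one half of the sample and none in the other. The pooled effect is 0.15 × 0.5 = 0.075, and the interaction is the same size. With N = 432, six cells and three covariates, λ = 432 × 0.075² = 2.43, df1 = 2, df2 = 432 − 6 − 3 = 423, and interaction power = 0.265. Such heterogeneity would be missed about 73% of the time (1 − 0.265). If the interaction itself were f = 0.15, power would be 0.80.

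**The case against.** The strongest reply is that this is a condensed article. Subgroup tables and interactions with a stratification factor are often left to the analysis plan, which is not shown and could contain them. The Discussion sentence can also be read as being about inclusion: parent report lets young children, and families receiving only parenting help, take part at all. Stratification does make a within-age comparison possible, and few trials are powered by stratum.

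Much of this stands, and it rules out several stronger readings that a reader might infer:

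- *That the trial commits itself to generalising to all ages.* The Participants section only expresses a wish, and the roll-out in the Discussion is conditional on the components proving effective.
- *That 49% power is a design failure.* It assumes an even age split that the document does not give, it is the power of a separate test within one stratum, and no such power is promised.
- *That the sample size allows for the pooled effect only.* It mentions possible interactions without naming them, so age cannot be excluded.
- *That two unrelated interventions are being pooled.* Both TSM forms deliver obstacle feedback plus support tools and share self-efficacy, supportive-relationship and alliance domains. Conditions 2 and 3 remain separate arms.
- *That generalisation could be made to depend on the two age groups agreeing.* Without a criterion, and with about 27% power in the illustration, that rule would reassure falsely.

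What the reply does not remove is the covariate rule. It is stated in the article, and it will probably leave out a stratification factor that also fixes the informant. Nor does the reply supply, anywhere in the text, an analysis or variable behind the Discussion claim.

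**Conclusion.** The concern holds in a limited form. The described analysis gives one effect averaged over parent report and self-report, probably without adjustment for informant. The statement about young children and parent-only help has no matching analysis. The randomisation, the primary comparison's validity and the sample size of 432 are not in question.

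For age-specific estimates the matter is one of precision: power of about 0.31 to 0.64 at f = 0.15 in the 4-11 group, and pairwise half-widths of about 0.42 to 0.28 residual SD against 0.23 pooled. These figures assume that 4-11 makes up 30% to 70% of the 432, with equal arms. Parent-only families are a smaller and, as described, unidentified subset, so their estimates would be weaker still. The size of the precision loss from omitting age group cannot be computed, because the article gives no SDQ variances by informant and does not name the three covariates.

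**What to change.** 1. **Statistical analyses.** Always include age group, which is also informant, in the SDQ total difficulties model, whether or not it differs between arms.
2. **Same section.** Name condition by age group in advance as an exploratory term. Report condition contrasts with 95% CIs overall, for 4-11 (parent report, TSM-P) and for 12-17 (self-report, TSM-Y). State that a non-significant interaction will not be taken as proof that the effect is the same at all ages.
3. **Strengths and limitations.** Say that there is one informant per client, set by age, and that age-specific estimates are exploratory and imprecise, giving the power range above with its assumption.
4. **Parent-only help.** Delete the claim, or limit it to a descriptive report if the patient file identifies these families in all three arms.

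Cost: two model terms on a factor already recorded for randomisation, one table and some rewording. No new questionnaires or clients are needed. The downside is one extra exploratory comparison with wide intervals.

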### Implications for practice

By investigating several potentially effective components of feedback from ROM in youth mental health care, we contribute to the identification of important aspects of feedback and to a better understanding of possible mechanisms underlying feedback effects (e.g. what works for whom, when and how). We also contribute to the knowledge about and possibilities for use of feedback in the real world, through which the results of our study will be immediately relevant for clinical practice. Moreover, we extend the knowledge to youth mental health care in the Netherlands.

If the different components of feedback prove to be effective, the study will have strong practical relevance because the results will help to support the care for youth and to improve the treatments that children, adolescents and their parents receive. Clinicians might be better able to track the course of everyday treatments, signal potential treatment failures and adjust treatments accordingly by discussing the feedback with their clients. Eventually, treatments might have better outcomes, might contain fewer sessions and might become shorter. Also, children, adolescents and parents might drop out of treatment less often and might be more satisfied at the end of treatment. Consequently, there is potential for roll-out of the feedback with the most effective components across all youth departments of mental health care institutions throughout the Netherlands.

## Endnote

^a^Parents/caregivers might refer to any people who care for children and adolescents, e.g. biological parents, stepparents, adoptive parents, grandparents, other family members or guardians. Because children and adolescents are generally referred to mental health care with their biological parents or stepparents, we use the term ‘parents’ in the remainder of the study protocol.

## Abbreviations

ROM: Routine Outcome Monitoring; NOT: Not On Track; TSM-Y: Treatment Support Measure–Youth Form; TSM-P: Treatment Support Measure–Parent Form; SDQ: Strengths and Difficulties Questionnaire; RCI: reliable change index.
